### Recruitment {15}

The research will take place during the 2022 National Influenza Immunization Campaign, held starting in April. Participants will be recruited in the waiting room while waiting to be vaccinated. An assistant researcher will initially approach the participant and orient them to the research objectives and invite them to participate.

## Assignment of interventions: allocation

### Sequence generation {16a}

The randomization process will be carried out by a researcher external to the study, through the website (http://www.randomization.com/). Seven blocks of 50 people will be generated, with the permutation of the two groups (control group and intervention group). The randomization will be carried out in blocks, because if there is any problem during the study and it is necessary to interrupt it, it will be easier to obtain a balance between the number of participants in each group.

### Concealment mechanism {16b}

After the randomization generation, the same external researcher will distribute the random sequence of participants in each group, in sequentially numbered envelopes, opaque and sealed. The confidentiality of each patient’s allocation will be disclosed to the researchers responsible only at the moment of vaccination administration, when the respective envelopes are opened.

### Implementation {16c}

At the time of vaccine administration, the envelope will be opened by the principal investigator to learn how the IM administration of influenza vaccine will be performed (using or not the portable vibration device in associate with cryotherapy).

## Assignment of interventions: blinding

### Who will be blinded {17a}

The study will be of the open, unblinded type, since it will not be possible for the participant and the researcher to be unaware of the presence or absence of the portable vibration device associated with cryotherapy.

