### Intervention description {11a}

Patients will be randomized and assigned to one of two groups: control group (CG) or intervention group (IG). They will remain in these groups until the end of the study.CG: participants who will receive the influenza vaccine by IM as per the standard protocol of the service, without the use of any intervention for pain relief and anxietyIG: participants who will receive the influenza vaccine by IM route using the portable high-frequency vibration device associated with cryotherapy for 30 s before application and during administration of the vaccine. The reusable plastic handheld device called Buzzy® has a reusable ice pack (cryotherapy) and a button to trigger the high-frequency vibration. The device is based on the pain gate control theory by using the non-painful stimuli of cold and high frequency vibration on the deltoid before and during vaccine administration to inhibit the transmission of painful stimuli [19]

The research will take place during the 2022 National Influenza Immunization Campaign, starting in April. The principal investigator will be responsible for administering the influenza vaccine to all participants in both groups.

The influenza vaccine consists of inactivated, fractionated, and purified viruses, characteristics that ensure that it does not cause the disease. The immunobiological distributed free of charge by the Ministry of Health will be used. The influenza vaccine (fragmented, inactivated) is an injectable suspension composed of different strains of the inactivated, fragmented, and purified Myxovirus influenzae virus, A/Victoria/2570/2019 (H1N1)pdm09; A/Darwin/9/2021 (H3N2); B/Austria/02/1359417/2021 (linhagem B/Victoria).

In both groups (control and intervention), the participants will be seated, in an air-conditioned environment, and will receive guidance about the procedure and possible adverse events. If there is no contraindication, the participants can choose which limb they want to receive the vaccine in (right or left deltoid). The researcher will perform hand hygiene and help with the correct positioning, keeping the forearm of the selected limb over the abdomen, with the aim of relaxing the shoulder.

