IG: The researcher will check the integrity of the immunizer liquid and expiration date of the vial with the participant. The researcher will clean the rubber of the vial with dry cotton and will attach a 25 × 7.0 dec/mm needle to the 1 ml sterile syringe and insert it into the vial. He will homogenize the liquid and then aspirate 0.5 ml of immunizer, as directed by the Health Ministry. After aspiration of the immunizing liquid, the needle will be replaced by a 2 5mm × 0.6 dec/mm needle. An assistant researcher will remove the ice pack (cryotherapy) from the freezer at the moment of vaccine administration and will attach it to the portable vibration device. The button to trigger the vibration will be turned on, the device will be attached to the site where the vaccine will be administered (deltoid muscle) and will remain for 30 s. The device’s dwell time will be timed, using a Vollo® digital stopwatch with alarm. After this time, the attached device will be slid about 2 cm above the administration site and the vaccine will be administered by the principal investigator. The 25 mm × 0.6dec/mm needle, attached to the syringe, will be inserted fully into the deltoid muscle at a 90° angle to the skin of the arm, and then the vaccine will be administered quickly to reduce the time the needle remains in the muscle. The needle will be removed at a 90° angle while the researcher lightly presses the muscle with a cotton swab. After complete removal of the needle, compression will be maintained at the application site, without massage, for approximately 30 s. The handheld device will be turned off and removed from the limb. Local reactions such as bleeding will be evaluated. If present, compression will be maintained until the bleeding stops completely, and an antiseptic bandage will be applied. The assistant researcher will disinfect the portable high-frequency vibration device and the ice pack with 70% alcohol. The ice pack will be returned to the freezer for later use.

After vaccine administration, the syringe and needle packaging will be discarded in regular trash containers and the vaccine bottle in an appropriate place, according to legislation. The researcher will perform hand hygiene and sign the full name legibly on the vaccine card and return it to the participant, who will be instructed to remain on the premises for 15 minutes to observe for possible adverse events.

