### Procedure for unblinding if needed {17b}

Not applicable, because this study has no blinding step.

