## Data collection and management

### Plans for assessment and collection of outcomes {18a}

Before vaccination, an auxiliary researcher will collect data on sociodemographic characterization such as age, gender, and education. Baseline data on the primary outcomes will also be obtained: level of pain expected with the vaccine, from the previously validated Numerical Scale from 0 to 10 [23] and pre-vaccine anxiety level, from the previously validated visual analog anxiety scale, in which they should mark the anxiety level along a horizontal line, containing a scale from 0 to 10 [22, 24].

After vaccination, another assistant researcher will collect the data on pain and anxiety levels after vaccination, for comparison with the values previously collected (baseline) and also for comparison between the groups, control and intervention. The levels of pain and anxiety after vaccination will be obtained from the same instrument used in the pre-vaccination step.

In addition, information will be collected on satisfaction with vaccine administration, measured on a 10-point Likert scale, where 0 = totally dissatisfied and 10 = highest possible satisfaction) [22]. The IG participants will also be asked about the discomfort caused by both the temperature of the frozen bag in contact with the skin and the vibration of the device in contact with the skin, both will be evaluated by a Likert scale in which 0 = “not at all” and 10 = “extremely uncomfortable” [22].

Auxiliary researchers will participate in a training session to perform data collection, based on realistic simulation.

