### Data management {19}

The data generated by the study will be collected on paper forms and stored for a period of 5 years. The data will be entered independently into spreadsheet software by two auxiliary researchers. The database will be checked by the principal investigator and then exported to the *Statistical Package for Social Science* (SPSS) version 22.0 software. The clinical trial data will be managed and analyzed by one of the researchers who will not participate in the recruitment and intervention to ensure the authenticity, integrity, and privacy of the data during the research process.

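### The reason given for no blinding covers only the participant and the vaccinating team; the post-vaccination collector and the analyst could be kept unaware of allocation, and the denial of any blinding step conflicts with the data monitoring committee section

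*Protocol article*

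**What the plan says.** Who will be blinded {17a} gives both the decision and its only reason: "The study will be of the open, unblinded type", on the ground that neither the participant nor the researcher can be kept from knowing whether the device is used. Procedure for unblinding {17b} follows with "Not applicable, because this study has no blinding step". The Discussion repeats the reason as a limitation and ties it to the moment of vaccine administration.

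The roles are described elsewhere:
- Injection, Intervention description {11a}: "The principal investigator will be responsible for administering the influenza vaccine to all participants in both groups".
- Device, same section: "An assistant researcher will remove the ice pack (cryotherapy) from the freezer at the moment of vaccine administration". That assistant also attaches the pack and disinfects the device afterwards.
- Outcome collection {18a}: one assistant takes the baseline data, and then "After vaccination, another assistant researcher will collect the data on pain and anxiety levels after vaccination". The same item has intervention-group participants also rate discomfort from the cold and from the vibration.
- Data management {19}: the data are "managed and analyzed by one of the researchers who will not participate in the recruitment and intervention". The purposes given are authenticity, integrity and privacy; concealing the arm is not among them.
- Data monitoring committee {21a}: its monitoring and analysis of the data are described as blinded.

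**The concern.** The protocol takes a reason that applies to the people at the injection and applies it to the whole study. Two roles that need not see the device, the post-vaccination collector and the analyst, are left without any statement that they are kept unaware of allocation.

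The primary outcome is a subjective score from 0 to 10, and Sample size {14} plans on a pain difference of only 0.25 points. A collector who knows the arm can influence how the question is put and how the answer is written down. An analyst who sees the arms makes the remaining analysis decisions knowing which way each one moves the result. Statistical methods {20a} leaves some of these loosely described, notably the use of secondary outcomes as covariates for pain and the associations with sociodemographic characteristics.

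There is also a plain inconsistency: {17b} says that there is no blinding step, and {21a} describes one.

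**Working it through.** No stated figure is in dispute, so the main check sets the roles against the reason in {17a}.

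| Role | Source | Must this person know the arm? |
|---|---|---|
| Participant | {17a} | Yes |
| Injector (principal investigator) | {11a} | Yes |
| Device assistant | {11a} | Yes |
| Baseline collector | {18a}, Table 1 | No; baseline data are taken at enrolment, before allocation |
| Post-vaccination collector | {18a} | No, unless also the device assistant |
| Analyst | {19} | No, if the data file does not show it |
| Data monitoring committee | {21a} | Described as blinded |

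**Collector.** Item {18a} separates this person from the baseline collector only. Nothing says that the collector differs from the device assistant of {11a}. If they are the same person, the collector cannot be blinded. The discomfort items, asked of one arm only, would also reveal the arm if they came before the pain, anxiety and satisfaction scores. The trial controls that order.

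**Analyst.** Coded arm labels alone would not work. The two discomfort columns would be filled in one coded arm and empty in the other. They would have to be withheld. The primary between-group comparison loses nothing by this, because variables that exist in one arm only cannot enter it.

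**Illustration of scale.** The documents give no size for collector influence, so the shift below is an assumption.

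Inputs: 350 participants, so 350 / 2 = 175 per arm ({14}); target difference 1.12 − 0.87 = 0.25 ({14}); two-sided 5% test (sidedness is not stated, so assumed); no true effect; a between-arm shift b = 0.1 point (assumed), which is 0.1 / 0.25 = 40% of the target.

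Formulas: SE = SD × √(2/175) = SD × 0.1069; z = b / SE; rejection rate = 1 − Φ(1.96 − z) + Φ(−1.96 − z).

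| Assumed SD of the pain score | SE | z | Rejection rate |
|---|---|---|---|
| 1.5 | 0.160 | 0.62 | 0.096 |
| 1.0 | 0.107 | 0.94 | 0.155 |
| 0.50 | 0.053 | 1.87 | 0.46 |

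The SDs printed in {14}, 0.07 and 0.10, are not used. They give a standardised difference of 0.25 / √((0.07² + 0.10²)/2) = 0.25 / 0.0863 = 2.90, for which a t-test calculation needs 4 per group, not the stated 86. The last row uses the SD that 86 per group would imply: at 90% power and two-sided 5% that size corresponds to a standardised difference of about 0.50, and 0.25 / 0.50 = 0.50.

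**The case against.** The strongest objection is that the participant is the assessor. Pain is self-reported and the participant cannot be blinded, so expectation bias remains whoever holds the form. Anxiety is already marked by the participant on a line, collectors are trained by simulation, data are entered independently by two people, and the Discussion admits the lack of blinding. All of this stands. It limits the benefit to prompting and recording by the collector and to influence by the analyst.

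A reader might infer that nobody in the trial is blinded. The document does not support that: {17a} names only the participant and the researcher, and {21a} calls the committee's work blinded.

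A reader might also infer that the staffing for a blinded collector is already in place. It is not stated, because the collector is separated only from the baseline collector.

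It is tempting to say that an analyst who sees the arms could choose freely between the t test and the Mann-Whitney test. Outcomes {12} and {20a} tie that choice to a normality test. With a mean near 1 and an assumed SD of 1.0, a Poisson-like score has about 37% zeros, against 16% below zero under a normal curve. That gap of 0.21 exceeds the 5% Kolmogorov-Smirnov limit of about 1.36/√175 = 0.10. Normality would then be rejected whether or not the arms were visible. Analyst latitude lies in the less defined covariate and association analyses.

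Finally, room layout, page order and file coding are details that an article may leave to the full protocol. That is fair for the details. It does not cover an explicit statement that there is no blinding step, resting on a reason that does not reach two of the roles.

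**Conclusion.** The point holds in limited form, as a cheap improvement and not as a flaw that undermines the trial. The reason in {17a} justifies open conduct for the participant and the vaccinating team only. The post-vaccination collector and the analyst could be kept unaware of allocation, on two conditions: the collector is not the device assistant, and the analyst's file omits the discomfort columns. Separately, {17b} and {21a} contradict each other.

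The size of the removable bias is unknown. The false-positive rates of about 10% and 15% (SD 1.5 and 1.0), and 46% at SD 0.50, show what a 0.1-point shift would do from whatever source. A reader might take them as the bias to be expected from an unblinded collector; the documents give no evidence that such a shift would occur, or that blinding would remove all of it. Participant expectation would remain in any case.

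**What to change.** - In {17a}, state that participants and the vaccinating team are unblinded, and that the post-vaccination collector and the analyst are not told the allocation.
- State that the collector is not the device assistant and stays out of the vaccination step. The baseline assistant, whose data are complete before the envelope is opened, could handle the device, so no one need be added.
- Have participants mark pain, anxiety and satisfaction themselves before the intervention-only discomfort items are opened.
- Give the analyst coded arm labels, with the two discomfort columns withheld until the primary between-group pain analysis is final.
- Reconcile {17a}, {17b} and {21a}, saying what the committee is and is not blinded to.

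The cost is minor logistics: where the collector sits, the order of the form, how the file is prepared, and rostering the baseline assistant when the clinic is busy. Some participants may still reveal their arm to the collector. Sample size and trial procedures do not change.

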### Procedure for unblinding if needed {17b}

Not applicable, because this study has no blinding step.

## Data collection and management

### Plans for assessment and collection of outcomes {18a}

Before vaccination, an auxiliary researcher will collect data on sociodemographic characterization such as age, gender, and education. Baseline data on the primary outcomes will also be obtained: level of pain expected with the vaccine, from the previously validated Numerical Scale from 0 to 10 [23] and pre-vaccine anxiety level, from the previously validated visual analog anxiety scale, in which they should mark the anxiety level along a horizontal line, containing a scale from 0 to 10 [22, 24].

After vaccination, another assistant researcher will collect the data on pain and anxiety levels after vaccination, for comparison with the values previously collected (baseline) and also for comparison between the groups, control and intervention. The levels of pain and anxiety after vaccination will be obtained from the same instrument used in the pre-vaccination step.

In addition, information will be collected on satisfaction with vaccine administration, measured on a 10-point Likert scale, where 0 = totally dissatisfied and 10 = highest possible satisfaction) [22]. The IG participants will also be asked about the discomfort caused by both the temperature of the frozen bag in contact with the skin and the vibration of the device in contact with the skin, both will be evaluated by a Likert scale in which 0 = “not at all” and 10 = “extremely uncomfortable” [22].

Auxiliary researchers will participate in a training session to perform data collection, based on realistic simulation.

### Plans to promote participant retention and complete follow-up {18b}

Because this is a one-time intervention, there will be no follow-up period, which reduces the possibility of discontinuity. The outcomes will be measured in two moments: before and immediately after vaccination. Participants who drop out of the study and do not submit responses about pain and anxiety levels before and after vaccination will not be included in the study.

### Data management {19}

The data generated by the study will be collected on paper forms and stored for a period of 5 years. The data will be entered independently into spreadsheet software by two auxiliary researchers. The database will be checked by the principal investigator and then exported to the *Statistical Package for Social Science* (SPSS) version 22.0 software. The clinical trial data will be managed and analyzed by one of the researchers who will not participate in the recruitment and intervention to ensure the authenticity, integrity, and privacy of the data during the research process.

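### The check of the database before export is given to the principal investigator, who opens every envelope and gives every injection, and this fits poorly with the plan's own promise of independent data management

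*Protocol article*

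**What the plan says.** The protocol article deals with data handling in Data management {19}. Outcomes are recorded on paper forms, which are kept for 5 years. On entry it says: "The data will be entered independently into spreadsheet software by two auxiliary researchers". It continues: "The database will be checked by the principal investigator and then exported" to SPSS. The next sentence reads: "The clinical trial data will be managed and analyzed by one of the researchers who will not participate in the recruitment and intervention", and the reason given is "to ensure the authenticity, integrity, and privacy of the data during the research process".

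The principal investigator's other tasks appear elsewhere:

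- Intervention description {11a}: "The principal investigator will be responsible for administering the influenza vaccine to all participants in both groups".
- Implementation {16c}: at vaccination, "the envelope will be opened by the principal investigator".
- Who will be blinded {17a}: "The study will be of the open, unblinded type".

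The section on the coordinating centre {5d} also describes the data management team (professors) separately from the execution team (nurses and nursing students).

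**The concern.** The plan claims one protection for its data after collection: they are handled by a person who neither recruited nor treated anyone. Checking an entered database is ordinarily part of data management, and the article describes it under that heading. Yet the check goes to the one person who knows every allocation and delivered every injection.

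The step matters because double entry only detects disagreements, and someone must then decide which value stands. The only check the article names before export is the principal investigator's. The outcomes are subjective ratings on paper, and anxiety is a mark on a line that has to be read off. An analyst who starts after export receives values already settled, so independence at that stage cannot make up for its absence one step earlier.

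**Working it through.** No figure in the plan depends on this point, so there is nothing to recompute. The check is a comparison of who does what.

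| Step | Who | Section |
|---|---|---|
| Opens the envelope | Principal investigator | Implementation {16c} |
| Vaccinates, both arms | Principal investigator | Intervention description {11a} |
| Collects pain and anxiety ratings | Assistant researchers | Plans for assessment {18a} |
| Enters data, twice and independently | Two auxiliary researchers | Data management {19} |
| Checks the database before export | Principal investigator | Data management {19} |
| Manages and analyses | Researcher outside recruitment and intervention | Data management {19} |

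1. **Is the checker someone the safeguard excludes?** Yes. The safeguard is defined by non-participation in recruitment and intervention, and the principal investigator carries out the intervention for every participant.

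2. **Is the check part of data management?** By its place in the article, yes. On a strict reading, the two sentences then assign the same function to two people, one of whom does not meet the condition. On a sequential reading, management by the independent researcher begins only after export. The sentences are then compatible, but the safeguard does not cover the pre-export check. The text does not say which reading is meant. On either one, the principal investigator holds that step.

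3. **Could the checker tell the arm of a record?** Yes, by three routes. The principal investigator learned each allocation at vaccination. Under Confidentiality {27}, participants are identified by initials and a number that follows the order of allocation, so records can be matched to injections. Under Secondary outcomes, the cold and vibration discomfort ratings come only from the intervention group, so whether those fields are filled or blank shows the arm.

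4. **What follows for a remedy?** Because of the third route, withholding the arm column alone would not mask whoever does the check. The two discomfort items must be separated as well.

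**The case against.** The strongest case on the other side is that the Data management section describes a sequence: double entry, a check, export, then independent management and analysis. All of these statements can be true together, so calling them a flat contradiction goes too far. That stands, and the point is therefore put as a poor fit.

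A reader might also infer that the principal investigator will settle unclear marks, edit values or decide which records are unusable. The article does not say so. It says only that the database is checked. The exclusions under {18b} and {20c} concern participants who withdraw and do not submit responses, not a checker's judgement. Edit rights and audit trail are details that an article commonly leaves to fuller documents, and their absence is not criticised here.

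Several safeguards limit the harm. Assistant researchers collect the outcomes, entry is double and independent, the retained forms allow a changed value to be traced, and the primary outcome is a 0 to 10 number that leaves little to interpret. The participants, who rate their own pain, know their arm, and the article names the lack of blinding as a limitation. The risk added by the check is probably small beside that. The data monitoring committee is a weaker answer, since its section {21a} gives it monitoring and analysis of the data and does not mention checking or correcting the database.

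It is also tempting to put a size on the harm by setting an assumed shift against the planning differences in Sample size {14}: 1.12 − 0.87 = 0.25 points for pain and 1.53 − 1.48 = 0.05 for anxiety. The document supports no value for such a shift. The anxiety difference also runs against the device (1.53 with it, 1.48 without), so it cannot serve as a yardstick for bias in the device's favour.

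What survives is that the article expressly gives this step to a person outside its own definition of independence. That is a stated assignment, not an omitted detail.

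**Conclusion.** The point holds in a limited form. The article promises data management by someone outside recruitment and intervention, and leaves the last named step before export with the person who opens every envelope and vaccinates every participant. All 350 planned records would pass through that step.

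This is a modest and avoidable risk of bias in an open trial with self-reported outcomes. It does not show that data have been or would be altered, and no numerical magnitude can be derived. The conclusion rests on the role statements as written and on treating a pre-export check as part of data management. It does not require the two sentences to be irreconcilable. The change is worth making because it is cheap and makes the claimed safeguard true.

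**What to change.** Revise Data management {19} as follows:

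- The non-participating researcher already named there compares the two independent entries, resolves discrepancies against the paper forms and locks the file before export.
- During this work the arm code and the two intervention-only discomfort items are withheld, or are checked separately once the pain and anxiety values are settled. If these items share a sheet with pain and anxiety, they need a separate page or must be covered.
- The principal investigator answers only queries that the forms cannot resolve, and does not edit outcome values.

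The cost is a short rewording of one section, some care with form layout, and a small shift of workload to a person already on the team. No extra staff are needed, and the sample size and planned analyses do not change.
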